Although some studies have demonstrated methods to optimize asthma outcomes and minimize costs, this does not guarantee that patients actually receive the best care. It is estimated that across the spectrum of health care, 30-40% of patients do not receive treatments of proven effectiveness [22,23]. Studies from the United States have shown that primary care practitioners do not use preventive medications in up to 45% of children with asthma [24,25], and unpublished data (2008-2011) reported by *Alberta Health Services (AHS)* from Alberta pharmacies show that about 50% of children with asthma who are treated with rescue beta-agonists do not also receive preventative medications [26].

Clinical pathways are a common strategy for changing professional behavior and improving the quality of care delivery, reducing practice variation, and reducing costs of health care [27-30]. Although relatively few published studies have rigorously evaluated the impact of clinical pathways on clinical outcomes and costs [29], it is widely recognized that the rigor involved in pathway development and assessment of evidence obtained is important to improving outcomes. Accordingly, many health organizations such as AHS are using clinical pathways with this intent. In support of this approach, a clinical pathway focused on the emergency management of childhood asthma has been shown to increase the use of evidenced-based therapies [29,30]. However, creation of clinical pathways (or guidelines) is not enough; active implementation strategies are needed to achieve optimal improvements in outcomes [31-34]. Two strategies that are among the most consistently successful for changing practitioner behavior and improving patient outcomes are interactive educational sessions and reminder systems [31-34].

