Even if children are prescribed appropriate medications, parents frequently do not receive adequate information and education to understand the rationale and importance of using preventive medications, which often results in poor adherence [35-37]. *Adherence* refers to a patient successfully taking medication. *Primary adherence* refers to the obtaining of medication prescribed, and *secondary adherence* refers to proper completion of the regime as intended by the prescriber. A World Health Organization [38] review indicated 30% adherence to medications by children and adolescents with asthma, which is among the lowest reported for any chronic disease. There is good evidence, however, that asthma education programs for children with severe exacerbations requiring emergency department and in-hospital care sufficiently improve adherence to reduce subsequent hospitalizations, emergency department visits, and urgent disease-related physician visits by 20-30% [39].

We propose to improve the prescription and use of evidenced-based preventative therapies for children with asthma, with the goal to significantly improve their disease control and quality of life, and reduce unnecessary emergency department visits and hospitalizations by 20% each. We will achieve this by (1) installing a primary care clinical pathway for managing childhood asthma into clinicians’ electronic medical record (EMR) to facilitate the use of best evidence by practitioners, and (2) training chronic disease management (CDM) health professionals to provide targeted and timely asthma education to parents and children with asthma. We will test this pathway and education project in a representative sample of 22 Alberta primary care practices, using a pragmatic cluster-controlled trial methodology. Specifically, we will determine if our proposed innovation, as compared with usual care,...

...increases *prescription* of evidenced-based preventative therapies;...increases *dispensing* (primary adherence) of evidenced-based preventative therapies;...improves children’s *asthma control*;...improves *quality of life* for children and families; and...decreases *health care utilization* (emergent primary care visits, emergency department visits, and hospitalizations) for asthma, and decreases overall societal (health system and family) costs.

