### Economic Analysis

The potential for provincial-wide savings is achievable because of the high-quality evidence (numerous randomized controlled trials, systematic reviews, and international consensus guidelines) demonstrating that appropriately tailored anti-inflammatory medications reduce emergency department visits and hospitalizations and that asthma education training targeted to focus on families with children with more severe disease also yields a 20% reduction in subsequent hospitalizations, a 30% reduction in emergency department visits, and a 30% reduction in nonscheduled urgent physician visits for disease exacerbation [39]. Further validating the ability of preventative therapy for asthma to reduce health care utilizations and costs, health services studies in children and adults in both British Columbia and Sweden utilizing administrative data have shown that higher utilization of inhaled corticosteroids is correlated with lower rates of hospitalization and lower overall health care costs [60,61].

The primary analysis will be from the health care system perspective. Total health system costs per child with asthma in the 2 trial arms before and after the intervention will be determined. Health system costs will be disaggregated into the following three parts: (1) those stemming from pathway implementation and train-the-trainer education sessions, 2) those from asthma education provided by CDM professionals, and (3) those from hospitalizations and emergency department and practitioner visits for asthma. Overall health system costs will be considered decreased by the project intervention if the cost decrease from reduced emergent physician visits, emergency department visits, and hospitalization outweighs the cost increase from pathway implementation and asthma education. The impact on costs will be considered alongside the impact on outcomes including quality of life. A secondary analysis will also include consideration of family costs that consist of parent loss of work, travel, or other out-of-pocket costs due the child’s disease.

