Costs stemming from health care utilization (drugs, hospitalizations, emergency department, and practitioner visits) will be derived from health administrative data. Actual costs are available from *AHS* for in-patient stays at Calgary and Edmonton Zone hospitals, and costs for other Alberta hospitals can be approximated using Institute of Health Economics (IHE) provincial estimates [62]. Emergency department visit costs will be determined using the IHE standard provincial estimates [62]. Surveys of staff and parents of children with asthma from each of the participating practices will provide cost estimates by collecting the following data: time spent on train-the-trainer sessions, staff time to educate families, and family quality of life measures, as well as out-of-pocket expenditures on their child’s disease.

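### The three-part cost breakdown and the cost-saving rule omit medication, which the costing paragraph lists and the intervention is designed to increase

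*Protocol article*

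**What the plan says.** All of the costing text is in the Economic Analysis section of the protocol article.

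- **Perspective:** "The primary analysis will be from the health care system perspective". Total cost per child with asthma is to be determined in both arms, before and after the intervention.
- **Breakdown:** the total is divided into three parts. The first is pathway implementation and training of the trainers, the second is education given by the chronic disease management professionals, and the third is "those from hospitalizations and emergency department and practitioner visits for asthma".
- **Rule:** costs count as decreased "if the cost decrease from reduced emergent physician visits, emergency department visits, and hospitalization" "outweighs the cost increase from pathway implementation and asthma education".
- **Costing inputs, next paragraph:** "Costs stemming from health care utilization (drugs, hospitalizations, emergency department, and practitioner visits) will be derived from health administrative data".

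Three other places bear on this. Background and Overview states the aim: "We propose to improve the prescription and use of evidenced-based preventative therapies for children with asthma". Quantitative Data includes pharmacy dispensing among the datasets to be linked. Project Objectives treats the intervention as successful if it either saves cost or improves quality of life for child and parent, and success leads to a scale-and-spread strategy.

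**The concern.** Preventer use is how the intervention is meant to work. Prescribing a preventer is the primary outcome and dispensing one is a secondary outcome. The Economic Analysis itself attributes part of the expected fall in emergency visits and hospital stays to anti-inflammatory medication. The rule therefore credits what the drugs are expected to save and gives their cost a weight of zero.

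The text also disagrees with itself: one paragraph costs drugs, and the paragraph before it has no place to put them.

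What is at stake is the statement that the intervention saves cost, which is one of two sufficient criteria for success. The effectiveness outcomes, the randomization and the sample size are not touched.

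**Working it through.** The article states no cost figure for this rule, so there is nothing to reproduce. The check has three steps.

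**1. The cost items side by side (Economic Analysis)**

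| Item | Three-part breakdown | Rule | Costing paragraph |
|---|---|---|---|
| Pathway and training | part 1 | cost side | staff surveys (training time) |
| Asthma education | part 2 | cost side | staff surveys (time) |
| Hospital stays, emergency visits | part 3 | savings side | administrative data |
| Practitioner visits | part 3 | savings side (emergent physician visits) | administrative data |
| Drugs | absent | absent | administrative data |

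**2. What the omission does to the rule**

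Let S be the savings on visits and hospital stays, I the implementation plus education cost, and D the net change in drug cost borne by the health system.

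- Rule as written: cost saving if S > I.
- Complete rule: cost saving if S > I + D.
- If D > 0, the two disagree when I < S ≤ I + D. The rule as written then declares a saving that is not there.
- If D = 0, they agree.
- If D < 0, they disagree when I + D < S ≤ I. The rule as written then misses a real saving.

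**3. How large D could be**

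Inputs from the article:

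- Background and Overview reports that "about 50% of children with asthma who are treated with rescue beta-agonists do not also receive preventative medications", so about 50% do receive them.
- Sample Size Calculation and Analysis gives a minimal clinically important difference of 20%, without saying whether it is absolute or relative. Absolute: 0.70 − 0.50 = 0.20. Relative: 0.50 × 1.20 − 0.50 = 0.10. That is 10 to 20 more treated children per 100 symptomatic children.

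Assumptions that are not in the article: a preventer cost c of 100 to 500 dollars per additionally treated child-year, and a health-system payer share s of 0 to 100%.

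Formula, per symptomatic child-year and before any offset: D = rise × c × s.

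| Rise | c | s = 0 | s = 1 |
|---|---|---|---|
| 0.10 | 100 | 0 | 0.10 × 100 = 10 |
| 0.10 | 500 | 0 | 0.10 × 500 = 50 |
| 0.20 | 100 | 0 | 0.20 × 100 = 20 |
| 0.20 | 500 | 0 | 0.20 × 500 = 100 |

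The range is 0 to 100 dollars. Two points on units:

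- The denominator here is the symptomatic subset, meaning children with a short-acting beta-agonist prescription, whereas the plan's costs are per child with asthma. If the rise in preventer use is no larger outside that subset, the figure per child with asthma is no larger.
- Cost arises when a drug is dispensed, so the rise has to be read as dispensed treatment. A prescription that is not filled adds nothing.

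**The case against.** The strongest reply is that drugs are already in the plan. They head the list in the costing paragraph, dispensing data are to be linked, and the stated target is total health system cost. On that view part 3 is only a shortened restatement, and a condensed article may leave the detail to a fuller document. This has some force: the authors may well have meant to count drugs. But the rule and its components are written out explicitly, and a reader who follows them leaves drugs out. That is a conflict within the text, not a detail left for later.

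The second reply concerns who pays. The analysis takes the health system's view. Families' medication purchases are surveyed to measure the burden on the family, and out-of-pocket costs enter the secondary analysis. To the extent that families or private insurers pay, leaving drugs out of the primary rule fits its perspective. This stands as a limit on the size of the problem. It is not a reason the article gives, and the article places drugs with health care utilization.

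Two stronger readings are tempting, and neither is supported:

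- *The result is always biased toward cost saving.* This needs a net rise in drug cost borne by the health system. Payer shares and savings on rescue or exacerbation drugs are not given, so D can be zero, and step 2 of the working shows that a negative D would reverse the error.
- *A cost-saving result triggers provincial rollout.* Project Objectives says that success leads to developing a strategy. The Discussion speaks of working with partners toward delivery if results are positive, but does not tie this to the cost rule. The Economic Analysis adds that costs will be weighed together with outcomes.

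**Conclusion.** The point holds. The breakdown and the rule omit medication, the adjacent paragraph includes it, and the omitted item is one the intervention is meant to move. Followed as written, the rule can declare cost savings wrongly whenever D > 0 and I < S ≤ I + D.

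The size cannot be computed from the documents. Under the assumed prices and payer shares, D is 0 to 100 dollars per symptomatic child-year before offsets from fewer rescue drugs. The upper end requires a 20-point rise, 500 dollars per child-year and full payment by the health system. The lower end is reached if the health system pays none of the cost. Nothing in the documents shows whether the cost conclusion would change.

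**What to change.** 1. Add medication as a fourth component of health system cost, taken from the linked pharmacy dispensing data by arm and period. Count all asthma drugs, so that any fall in rescue medication offsets the rise in preventers.
2. Restate the rule as the between-arm difference in total cost: implementation + education + medication + visits + hospitalizations.
3. Count the publicly paid share of drug cost in the primary health-system analysis, and the full drug cost in the secondary analysis that includes family costs. State the payer shares and unit prices used.
4. Make the breakdown, the rule and the costing paragraph list the same items. If drugs are meant to be outside the primary perspective, say so, give the reason, and remove the conflict.

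The cost is a change of wording, unit prices and payer shares to apply to data already planned for linkage, and a little more analysis. The cost result may turn out less favourable.

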### Ethics Approval

The protocol obtained approval from the Health Research Ethics Board at the University of Alberta (Edmonton, AB) on August 7, 2015, and the Conjoint Health Research Ethics Board at the University of Calgary (Calgary, AB) on September 23, 2015.

## Results

Practice recruitment began September 2015, and all study-related activities are expected to conclude March 2018 (see Multimedia Appendix 3 for a timeline of major objectives) with the following outcomes:

### Primary Outcome

The proportion of symptomatic children with asthma in the baseline and follow-up periods (separate calculations) who are appropriately treated with a preventer will be the primary outcome. The denominator will be the number of children who meet the case definition of asthma *and* receive at least one prescription for an inhaled short-acting beta-agonist (eg, salbutamol) during the applicable period. The numerator will be, of these children, the number of those who receive a prescription for inhaled corticosteroid, montelukast, a combination of inhaled long-acting beta-agonist and corticosteroid (ie, agonist + corticosteroid), or some combination of these 3 drugs in the same period.

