#### Pathway Implementation Strategies

Based on previous extensive experience in implementing clinical pathways [44-46] and best evidence available [32,33,47-49], two change strategies were selected to implement the proposed project: (1) an interactive online learning module to teach primary care practitioners about the evidence for treatment strategies in the clinical pathway, and (2) user-written software installed within practitioners’ EMR that will serve as a reminder system to facilitate improved patient documentation and management. We will also use the results of a study being conducted using the TDF to identify necessary modifications to our strategy for primary care practices randomized to the intervention arm [50].

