#### Development of EMR Embedded Pathway

The EMR prototype (developed in *Med Access* and currently being developed in *Wolf*) provides practitioners with dropdown menus to document key findings from medical history review and physical examination, classify patient’s disease phenotype to generate therapeutic recommendations, assess asthma control, generate a risk assessment, and print out asthma action plans and patient prescriptions.

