### Quantitative Data

Data will come from 3 sources, namely, health administrative sets, data extracted from participating practices’ EMR, and surveys of asthma control, quality of life, and socioeconomic factors. Health administrative datasets will include Alberta Patient Registry, emergency department visits (*National Ambulatory Care Reporting System*), hospitalization abstracts (*Discharge Abstract Database*), practitioners visits (*Alberta physician/NP claims*), and pharmacy dispensing (*Pharmaceutical Information Network*); these datasets are considered to be of good quality with accurate personal identifiers on more than 95% of records. As previously noted, EMR data using a validated case definition will be extracted for all children with asthma meeting the inclusion/exclusion criteria. This will provide individual categorical and continuous patient-level data such as patient demographics, encounter history, medication prescriptions, and comorbid disease. Also as previously noted, the *HQCA* will play a pivotal role in our trial as they will (1) receive the aforementioned datasets from *AHS*, Alberta Health, and *NAPCReN/SAPCReN*; (2) extract and link the necessary data using a separate file from the practitioners, which will contain patients’ *CPCSSN* identifier linked to their Alberta Health Care Number; (3) perform the planned analysis; and (4) provide the aggregated results to our research team.

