### Secondary Outcomes

#### Dispensed Preventative Therapies (Primary Adherence)

The proportion of applicable children in baseline and follow-up periods who are appropriately *dispensed* a preventer will highlight if there is a significant gap between prescriptions given and filled. The denominator will be the same as for the primary outcome but the numerator will be the number of these children who are *dispensed* 1 or more preventer medications from newly available PIN data.

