#### Electronic Medical Record Data

The *CPCSSN* and research team will develop and validate a case definition and case finding algorithm for identifying children with asthma in the *CPCSSN* practices. The *CPCSSN* EMR data will provide, for all eligible children, individual categorical and continuous patient-level data such as patient demographics, ICD9 codes, and medication prescriptions. For children evaluated in practices randomized to the pathway group, data will also include asthma phenotype and provision of asthma action plans.

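### Prescriptions for the primary outcome come from an EMR that the intervention alters in one arm, so better recording can appear as better prescribing

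*Protocol article*

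**What the plan says.** The Primary Outcome section builds both parts of the proportion from prescriptions. A child enters the denominator by meeting the asthma case definition and having to "receive at least one prescription for an inhaled short-acting beta-agonist (eg, salbutamol) during the applicable period". The numerator is "the number of those who receive a prescription for inhaled corticosteroid, montelukast" or a combination product, in the same period.

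That section does not name the data source. Two others do. Under Quantitative Data, EMR extraction supplies "individual categorical and continuous patient-level data such as patient demographics, encounter history, medication prescriptions, and comorbid disease". Under Electronic Medical Record Data, the network's EMR extract supplies "individual categorical and continuous patient-level data such as patient demographics, ICD9 codes, and medication prescriptions". The only pharmacy source listed, the provincial pharmacy network, holds dispensing records.

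The intervention acts on that same record. Under Pathway Implementation Strategies, the installed software "will serve as a reminder system to facilitate improved patient documentation and management". Under Development of EMR Embedded Pathway, the tool can "print out asthma action plans and patient prescriptions". The randomisation section states that usual-care practices get neither component.

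The secondary dispensing outcome takes its numerator from the pharmacy network, but "The denominator will be the same as for the primary outcome". Its stated purpose is to show whether prescriptions given go unfilled.

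**The concern.** The EMR is the measuring instrument for the primary outcome, and the trial modifies it after randomisation in one arm. If some prescriptions in ordinary practice do not reach the extracted EMR data, and the software brings more of them in, the recorded proportion can move in the intervention arm with no change in what clinicians prescribe. More practices or more children would not reduce such a bias.

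The other safeguards in the article do not deal with this. Comparing baseline with follow-up does not remove it, because the recording change starts with the intervention. The validation described under Foundational Activities tests who has asthma, not whether prescriptions are captured. A positive result is meant to lead to delivery across Alberta, so it matters whether a gain is in prescribing or in recording.

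**Working it through.** The article gives no capture rate, so there is no planned figure to reproduce. The calculations below show how a recording change would act.

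**Inputs**
- True preventer prescribing, p = 0.50 in both arms. This rests on the pharmacy figure in Background and Overview that about half of children treated with rescue beta-agonists receive no preventive medication.
- Per-child capture, s: the chance that a child prescribed a preventer has at least one such prescription in the extract. Assumed values: 0.90 or 0.85 in control, 0.95 in intervention.

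**1. Numerator only, denominator unaffected.** Recorded proportion = p × s.
- 0.90 vs 0.95: 45.0% vs 47.5%; false difference 0.5 × (0.95 − 0.90) = 2.5 points.
- 0.85 vs 0.95: 42.5% vs 47.5%; false difference 0.5 × (0.95 − 0.85) = 5 points.

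For scale, the article sets the minimal clinically important difference at 20% without saying whether this is absolute or relative. If it is relative to 50%, it is 0.20 × 50 = 10 points, and the false differences are a quarter and a half of it. If it is absolute, they are an eighth and a quarter.

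**2. Several prescriptions per child.** One recorded preventer prescription is enough. If the rates above applied to each prescription, and a child had two captured independently (an assumption), per-child capture would be 1 − (1 − s)².
- 0.90 vs 0.95: 0.5 × (0.9975 − 0.9900) = 0.4 points.
- 0.85 vs 0.95: 0.5 × (0.9975 − 0.9775) = 1.0 point.

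**3. Reliever and preventer missed together.** If capture is all-or-none for a child, a missed child leaves the denominator too. Control: (0.5 × 0.85)/0.85 = 50%. Intervention: (0.5 × 0.95)/0.95 = 50%. The false difference is 0.

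**4. Better capture of reliever-only children.** Suppose children with a preventer are fully recorded in both arms, and reliever capture in the others is 0.85 in control and 0.95 in intervention. Control: 0.5/(0.5 + 0.5 × 0.85) = 54.1%. Intervention: 0.5/(0.5 + 0.5 × 0.95) = 51.3%. The false difference is −2.8 points, against the intervention.

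**5. The prescribed-minus-dispensed gap.** Let a share d be dispensed a preventer in both arms, with the denominator unaffected. With capture of 0.85 vs 0.95, the apparent gaps are 42.5 − d and 47.5 − d, against a true gap of 50 − d. Under-recording narrows the gap in both arms. The gaps still differ between arms by 5 points, with no difference in filling.

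**The case against.** The strongest reply is that no passage shows control practices missing prescriptions. Both arms are drawn from practices that belong to, or are joining, networks whose EMR prescriptions are extracted routinely. The items that the tool documents are mainly history, examination, phenotype and asthma control. If control practices already write nearly all prescriptions in the EMR, the effect is small. This stands: the bias is possible, not demonstrated.

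The denominator argument also stands. A child is counted only with a recorded reliever prescription, so some of that child's prescribing already reaches the EMR. Steps 3 and 4 show that the net effect can vanish or reverse.

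Three stronger readings are tempting, and the documents do not support them:
- A reader might infer that the bias is certain and favours the intervention. The documents establish an instrument that differs by arm, but not how much capture changes or in which direction the proportion moves.
- A reader might infer that the plan would turn a recording artefact into apparent poor adherence. Within an arm, missed prescriptions narrow the prescribed-minus-dispensed gap and so hide non-filling. Only a comparison of gaps between arms could mislead in that way.
- A reader might count preventers prescribed outside the practice as part of the problem. They are missing from the practice record in both arms, so they do not in themselves show differential measurement.

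Finally, the dispensing outcome would reveal a prescribing gain without a dispensing gain. It is a real but partial safeguard, because its denominator still depends on EMR reliever prescriptions. A capture check might sit in an analysis plan that is not shown. The point here concerns what the article itself fixes: the source, the numerator and the shared denominator.

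**Conclusion.** The concern holds as a risk to the interpretation of the primary result. The recording instrument can change after randomisation in one arm, and nothing in the article separates better recording from better prescribing. The illustrative size is 2.5 to 5 points. It rests on 50% true prescribing, assumed per-child capture of 85% to 90% in control and 95% in intervention, and no capture effect on the denominator. It is smaller with several prescriptions per child or when reliever and preventer prescriptions are missed together, and it can change sign. The documents support neither a firm magnitude nor a firm direction. A low-cost check is worth adding; a different primary outcome is not required.

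**What to change.** 1. Tabulate, by arm and period, the share of children with a dispensed preventer who have a matching EMR prescription, and the same for a dispensed reliever. Compare the change from baseline between arms rather than the level, since unmatched items will include drugs prescribed elsewhere.
2. Pre-specify a co-reported sensitivity analysis of the primary outcome, with the preventer numerator and the reliever denominator both taken from pharmacy dispensing in the applicable period. Using the applicable period keeps children who first become symptomatic in follow-up, as the primary definition does.
3. State that a prescribing gain, or a between-arm difference in the prescribed-minus-dispensed gap, will be interpreted in the light of items 1 and 2 and not attributed to prescribing or filling alone.

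The cost is a few sentences of analysis plan and an additional run on data that the analysing organisation is already to link. The downside is that dispensing also reflects filling, so it is a blunter measure of prescribing. For that reason the analysis should inform interpretation and need not be a confirmatory gate.
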